### Sample size

To develop a prognostic prediction model, the required sample size may be determined by three criteria suggested by Riley *et al*^28^ For example, suppose a maximum of 200 parameters will be included in the prediction model and the Cox-Snell generalised R^2^ is assumed to be 0.01. A total of 377 996 patients will be required to meet Riley’s criterion (1) with global shrinkage factor of 0.95; this sample size also ensures a small absolute difference (Δ<0.05) in the apparent and adjusted Nagelkerke R^2^ (Riley’s criterion (2)) and ensures precise estimate of overall risk with a margin of error<0.001 (Riley’s criterion (3)). According to the Quality and Outcomes Framework, the prevalence of AF in England is 1.7%.^29 30^ Given an AF prevalence of 1.7%, only 6425 patients will be expected to develop AF from 377 996 patients. Within the CHS database, there are 2 159 663 patients. Therefore, the number of patients in the CPRD and CHS datasets with AF will provide sufficient statistical power to develop and validate a prediction model with predefined precision and accuracy.

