To ascertain whether the prediction model is transportable to geographies outside of the UK, we will externally validate its performance in the Clalit Health Services (CHS) database in Israel. As a result of the National Health Insurance Law, Israeli citizens are required to enrol in one of four payer-provider health funds and receive free basic healthcare. CHS provides health insurance coverage to 4.8 million insured members and about two-thirds of the population aged >65 years. CHS is recognised globally as the primary source of evaluation of COVID-19 vaccinations and therapies.^23–26^ All clinical information is coded in International Classifications of Diseases, Ninth Revision (ICD-9). Receipt of vital status from the Ministry of the Interior ensures 100% follow-up of mortality. We will include participants insured by Clalit with continuous membership for at least 1 year before 1 January 2019: 2 159 663 patients with 4330 of them having a new incident of AF (AF and/or atrial flutter (AFl)) in the first half of 2019.

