**Figure 2 F2:**
[figure not shown]
A schematic representation of a multivariable logistic regression model or random forest model using data from electronic health records to provide risk prediction for incident AF. AF, atrial fibrillation.

Preprocessed patient-level data in CPRD-GOLD will be randomly split into an 80:20 ratio to create derivation and internal validation (or training and testing) samples. The split ratio is not a significant factor, given the volume of the sample size. The model parameters and drop-out rate will be chosen through a grid search and 10-fold cross-validation will be used (ie, 10% of the training data will be randomly selected as the cross-validation set). The multivariable logistic regression model will be developed with backward model selection with Akaike information criterion.^37^ The prediction window will be set at 6 months, as this is considered in keeping with the logistical time frames for organising AF investigation at scale.

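### The sample-size paragraph uses the 1.7% prevalence of AF as if it were 6-month incidence, so the 6425 expected events are overstated (about 8.5-fold at the CHS incidence, 3- to 7-fold at a crude CPRD incidence)

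*Protocol article*

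**What the plan says.** The Sample size section applies Riley's three criteria. It opens with "suppose a maximum of 200 parameters will be included in the prediction model", adds that "the Cox-Snell generalised R^2^ is assumed to be 0.01", and obtains 377 996 patients under "criterion (1) with global shrinkage factor of 0.95". It says this number also meets criterion (2), because it "ensures a small absolute difference (Δ<0.05) in the apparent and adjusted Nagelkerke" R², and criterion (3), a margin of error below 0.001 for the overall risk. It then takes a 1.7% AF prevalence for England and concludes: "Given an AF prevalence of 1.7%, only 6425 patients will be expected to develop AF". The section ends by saying that the numbers with AF in CPRD and CHS are enough to develop and validate the model.

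Other sections define what is being predicted:
- Inclusion and exclusion criteria: patients with diagnosed AF or flutter at study entry are excluded.
- Prediction model outcome ascertainment: the outcome is a first diagnosis of AF or flutter after baseline.
- Prediction model development: "The prediction window will be set at 6 months".
- Data sources and permissions: CHS has 2 159 663 "patients with 4330 of them having a new incident of AF" or flutter in the first half of 2019. CPRD has about 2 million eligible patients, with over 200 000 having an AF record during follow-up.

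**The concern.** Prevalence is the share of people who already have the condition. Those people are removed from this cohort, so 1.7% cannot be the share who will develop AF, least of all within 6 months. The quantity needed is 6-month incidence among people free of AF, and the protocol gives one such figure, for CHS.

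Two things depend on it. The first is the event count offered in support of adequacy: 6425 events is about 32 per parameter. The second is the meaning of R² = 0.01. The largest Cox-Snell R² a model can reach depends on the outcome proportion and is small for rare outcomes. A value that is modest at 1.7% may be demanding at the true 6-month incidence, and the Sample size section gives no source for it. If R² is set too high, criterion (1) returns too small a sample and the promised shrinkage is not achieved at that size.

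**Working it through.** **Inputs from the protocol.** p = 200 parameters, R² = 0.01, S = 0.95, proportion 1.7% (Sample size); 4330 of 2 159 663 in CHS, and about 2 million CPRD patients with over 200 000 AF records (Data sources and permissions); 80:20 split (Prediction model development), giving about 1.6 million for training.

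**Assumptions made here.** Mean CPRD follow-up of 10, 15 or 20.9 years (the last is the whole study window; the protocol gives no mean), constant hazard, and R² at 5%, 10% or 15% of its maximum.

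**1. The protocol's own figures.**
- Criterion (1): n = p / [(S − 1) ln(1 − R²/S)] = 200 / [(−0.05) ln(1 − 0.01/0.95)] = 377 996. It reproduces, and no outcome proportion enters.
- Events: 377 996 × 0.017 = 6425.9, stated as 6425. It reproduces; 6425/200 = 32 per parameter.

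**2. Six-month incidence.**
- CHS: 4330 / 2 159 663 = 0.2005%.
- CPRD, crude: 1 − exp[0.5 × ln(0.9)/T], where 0.9 is the share without an AF record. T = 20.9, 15 and 10 years gives 0.25%, 0.35% and 0.53%.

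**3. Expected events and the ceiling on R².** Maximum R² = 1 − exp{2[φ ln φ + (1 − φ) ln(1 − φ)]}.

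| Proportion φ | Events in 377 996 | Per parameter | Overstatement | Maximum R² | 0.01 as share of maximum |
|---|---|---|---|---|---|
| 1.7% (protocol) | 6426 | 32 | – | 0.158 | 6% |
| 0.20% (CHS) | 758 | 3.8 | 8.5-fold | 0.0285 | 35% |
| 0.25% (CPRD, 20.9 y) | 952 | 4.8 | 6.8-fold | 0.0346 | 29% |
| 0.35% (CPRD, 15 y) | 1325 | 6.6 | 4.8-fold | 0.0456 | 22% |
| 0.53% (CPRD, 10 y) | 1986 | 9.9 | 3.2-fold | 0.0635 | 16% |

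**4. Criteria (2) and (3) at R² = 0.01.** Criterion (2) needs S ≥ 0.01/(0.01 + 0.05 × maximum R²): 0.56 at 1.7% and 0.875 at 0.20%, both below 0.95. The criterion (3) margin, 1.96 √[φ(1 − φ)/377 996], is 0.0004 and 0.00014. Both criteria hold at either proportion.

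**5. Criterion (1) with R² tied to its maximum.** Required n for S = 0.95, and the shrinkage found by solving the same formula for S at a fixed n:

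| φ | R² as share of maximum | Required n | S at 377 996 | S at 1.6 million |
|---|---|---|---|---|
| 0.20% | 15% | 887 000 | 0.89 | 0.97 |
| 0.20% | 10% | 1.33 million | 0.84 | 0.96 |
| 0.20% | 5% | 2.66 million | 0.73 | 0.92 |
| 0.25% | 15% | 731 000 | 0.91 | 0.98 |
| 0.25% | 10% | 1.10 million | 0.87 | 0.97 |
| 0.25% | 5% | 2.20 million | 0.77 | 0.93 |
| 0.35% | 15% | 554 000 | 0.93 | 0.98 |
| 0.35% | 10% | 832 000 | 0.90 | 0.97 |
| 0.35% | 5% | 1.67 million | 0.81 | 0.948 |
| 0.53% | 15% | 397 000 | 0.948 | 0.99 |
| 0.53% | 10% | 596 000 | 0.92 | 0.98 |
| 0.53% | 5% | 1.19 million | 0.86 | 0.96 |

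**6. Events in the planned samples.** At 0.20% to 0.53%, 1.6 million training patients give about 3200 to 8400 events and 0.4 million test patients about 800 to 2100. At 1.7% a reader would expect 6800 in the test set.

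**The case against.** The strongest defence is that the prevalence does not produce the required sample. Criterion (1) uses only the parameter count, R² and shrinkage; 377 996 reproduces exactly, and criteria (2) and (3) survive the lower incidence. That stands. A reader might infer that 377 996 was calculated wrongly, and the protocol does not support that. What is wrong is the event count, together with an R² that is not related to the outcome proportion.

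Second, the 8.5-fold figure carries Israeli incidence into the UK derivation set. That also stands. The only CPRD information is the crude count, which points to a higher incidence and a 3- to 7-fold overstatement. Mean follow-up shorter than 10 years would narrow it further (about 2.3-fold at 7 years, 1.6-fold at 5). The count is itself rough, because cohort composition and any prevalent records within it are unknown.

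Third, R² = 0.01 might be called implausibly high. At 0.20% it would need an AUROC of about 0.95 (normal linear predictor assumed), which is hard to square with the moderate discrimination the Introduction reports for existing models. At 0.53%, however, it is 16% of maximum, an ordinary choice, and the required n at 15% of maximum (397 000) is close to the stated figure. So implausibility is not established.

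Fourth, the paragraph is framed as an example, and nobody will fit the model on 377 996 patients. This limits the consequence. But it is the only justification given, and the section's closing claim of adequacy follows from it.

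**Conclusion.** The event count is wrong as written, because a prevalence has been used for 6-month incidence in a cohort that excludes prevalent cases. This holds whatever follow-up is assumed. The size is conditional: about 758 events instead of 6425 if CHS incidence applies to CPRD, or about 950–2000 under a constant hazard with 10–21 years of mean follow-up.

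R² = 0.01 is no longer clearly cautious at 16–35% of its maximum, and at the lower incidences 377 996 patients may not give shrinkage of 0.95. Both statements depend on the incidence and on the assumed share of maximum R².

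A reader might go on to conclude that the CPRD derivation sample is too small. The figures do not support that. With about 1.6 million training patients, before exclusions, shrinkage is about 0.96 or more at 10–15% of maximum at every incidence considered. It falls short (0.92–0.948) only at 5% of maximum with incidence of about 0.20–0.35%. The paragraph should be corrected, but the study's validity is not threatened.

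**What to change.** Rewrite the Sample size paragraph:

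1. Replace the 1.7% prevalence with 6-month incidence in AF-free patients, preferably the CPRD count, otherwise 0.20% from CHS labelled as a proxy.
2. State R² as a fraction of the maximum Cox-Snell R² at that incidence, with a sensitivity range (for example 5–15%).
3. Restate the required n, expected events and events per parameter.
4. Compare these with the 80% training set after exclusions, not with total patients or all patients with AF. If the lower R² values fall short of 0.95, say so or limit the number of candidate parameters.
5. State the 6-month events expected in the 20% test set, since the age, sex and ethnicity subgroups under Internal validation rely on them.

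The cost is one paragraph and one count from data already held. No new patients are needed, although the stated requirement will look less favourable.

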### Predictor variables

A systematic review has been conducted to establish predictor variables included in varying combinations by preceding prediction models developed to detect incident AF in community-based EHRs (online supplemental table 1),^31^ and supplemented with a literature search for variables associated with incident AF.

10.1136/bmjopen-2023-075196.supp1Supplementary data

Candidate variables include

Sociodemographic variables including age, sex and ethnicity (SocioEconomic Score and population sector will serve as surrogate for ethnicity in CHS).All disease conditions included in the patient’s record, including hospitalised diseases and procedures, such as other cardiovascular diseases, diabetes mellitus, chronic lung disease, renal disease, inflammatory disease, cancer, hypothyroidism and surgical procedures.Lifestyle factors including smoking status and alcohol consumption that are coded in structured Read codes.

Predictive factors will be identified using the appropriate codes, with Read codes for diagnoses and lifestyle factors. Code lists for predictors will be used from publications if available, otherwise, the CPRD code browser will be used and codes checked by at least two clinicians. The code lists for predictors in CPRD-GOLD will be adapted from CALIBER and HDR UK repositories or publications. If none are available from these sources then new code lists are developed using the OpenCodelists and checked by at least two clinicians. Diagnostic code lists will comprise the primary care coding system (Read codes), to ensure that only information readily available within a primary care EHR could be incorporated within the prediction model. Within CHS, the code lists for predictors will be developed using similar methods based on the medical records and coding of CHS, which also includes a validated chronic diseases registry.

Candidate variable data types are deliberately limited to ensure widespread applicability of the model given the reality of ‘missing’ data in routinely collected EHRs.^17^ Observations and laboratory results are not included. Ethnicity information is routinely collected in the UK NHS and so has increasingly high completeness,^32^ and we will include an ‘ethnicity unrecorded’ category where it is unavailable because missingness is considered informative.^33^ Ethnicity in a UK context does not directly translate to an Israeli context so sociodemographic surrogates will be used: (1) population sectors—General Jewish, ultra-orthodox Jewish and Arab and (2) Socioeconomic score on a scale of 1–10. For diagnoses, if a medical code is present in the patient record (without a preceding time window limitation) then the variable is classified as being present for the patient. If medical codes are absent in a patient record we will assume that the patient does not have that diagnosis, or that the diagnosis was not considered sufficiently important to have been recorded by the GP in case of symptoms.^34^ Concordantly, the analytical cohorts are not expected to have missing data for any of the predictor variables. It is possible that diagnoses may be recorded as free text, data to which we do not have access, rather than as diagnostic codes and this may lead to misclassification of some patients.

### Data analysis plan

#### Data preprocessing

The CPRD-GOLD and CHS data will be cleaned and preprocessed for model development, internal validation and external validation. Specifically, for patient features with binary values, 0 and 1 will be mapped to the binary values. Variables with multiple categories (ethnicity) will be split into their component categories, and each given a binary value to indicate the presence or not of the variable for each patient. Continuous variables (age) will be kept as continuous.

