### Inclusion and exclusion criteria

The study population for derivation and internal validation will comprise all available patients in CPRD-GOLD eligible for data linkage and with at least 1-year follow-up in the period between 2 January 1998 and 30 November 2018. For the external validation, the study population will comprise participants insured by CHS, including those with continuous membership for at least 1 year, before 1 January 2019. Patients will be excluded if they were ≤30 years of age, or diagnosed with AF or AFl at the point of study entry, registered for less than 1 year or, in CPRD, ineligible for data linkage. Patients younger than 30 years of age are not included in the cohort for AF prediction because the incidence of AF over even a 10-year horizon is very low in this group.^1^

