#### Prediction model development

We will compare a machine learning and logistic regression approach to prediction model development for incident AF in CPRD-GOLD. Logistic regression model offers a more manageable approach for implementation, interpretation and training compared with machine learning algorithms, but machine learning methods can better handle non-linearities and interactions among variables and may lead to better discriminative performance.^19^

We will investigate the use of a random forest (RF) classifier for AF prediction in the CPRD-GOLD dataset. In our systematic review of AF prediction in EHRs, it had the most evidence for use and showed robust performance in different datasets and geographies.^19^ RF is an ensemble technique that combines a large number of decision trees using a bagging approach to improve the overall performance (figure 2).^35^ In brief, the bagging approach grows multiple classification trees in parallel where each tree gives a classification which is called votes. These votes are then aggregated to provide a more accurate and stable prediction. Furthermore, the degree of variation of each feature in an RF classifier for the prediction task can be calculated using the mean decrease in the Gini coefficient, a measure of how each variable contributes to the homogeneity of nodes and leaves in the resulting RF. Showing the importance of variables used in prediction (explainability) is considered important for clinical uptake of prediction models,^36^ and a limitation of using deep learning techniques. The RF model will be trained in the training dataset to predict a binary classification of developing AF or not. The model will return the probability between 0 and 1 for developing AF in the training set, corresponding to the predicted probabilities of developing AF.

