### Prediction model calculator

The full models are developed to take advantage of rich longitudinal community-based EHRs present in many high-income countries. However, there are other geographies (low-lower-middle-income countries) and care settings (emergency care, secondary care clinics) where searching for AF may be desired and an easy-to-use, simple model is preferable. From the derived prediction model, we will generate a parsimonious model based on factors with clinical rationale to predict new-onset AF over a 6 months time horizon.^9^ This will be based on the same core principles as detailed above, but use logistic regression to ensure transparency in how prediction results are calculated. We will aim to develop a user-friendly version of a model that may be applied as a calculator in a clinical and public setting, yet have good model performance indices.

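### As written, age enters the logistic model and the calculator as a single linear log-odds term; a pre-specified spline would guard against miscalibration by age at almost no cost

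*Protocol article*

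**What the plan says.** Four parts of the protocol article bear on how age enters the logistic models.

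- **Data preprocessing** sets the coding of all features: binary variables as 0/1, ethnicity as indicators, and "Continuous variables (age) will be kept as continuous".
- **Prediction model development** contrasts the two approaches and says that "machine learning methods can better handle non-linearities and interactions among variables and may lead to better discriminative performance".
- The same section, after Figure 2, gives the logistic build: "The multivariable logistic regression model will be developed with backward model selection with Akaike information criterion".
- **Prediction model calculator** says that the parsimonious model follows the same principles but will "use logistic regression to ensure transparency in how prediction results are calculated".

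None of them names a spline, polynomial, transformation or interaction, and none rules one out. Age is the only continuous predictor named, since under Predictor variables "Observations and laboratory results are not included". (The Israeli data also carry a socioeconomic score from 1 to 10.) The age range is wide: "Patients will be excluded if they were ≤30 years of age", with no upper limit stated.

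**The concern.** Backward selection starts from the terms it is given and drops some of them. If the starting set holds age as one continuous variable, the selected model has age as one linear log-odds term or no age term at all. A random forest can follow a curved age effect without being told to.

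Two things are at stake. First, if AF log-odds are not linear in age, the logistic model and the calculator built on the same principles would give absolute risks that are wrong in a pattern that depends on age. The calculator is meant for clinical and public use. Second, the head-to-head comparison would partly measure one coding decision rather than the two methods. The measures exposed are those that depend on absolute risk: calibration, Brier score, reclassification at the average 6-month incidence, and decision curves.

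**Working it through.** **1. The plan's own figure.** Sample size assumes p = 200 parameters ("suppose a maximum of 200 parameters will be included in the prediction model"), shrinkage S = 0.95 and Cox-Snell R² = 0.01. Riley criterion 1 is

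n = p / [(S − 1) · ln(1 − R²/S)] = 200 / [(−0.05) · ln(1 − 0.01/0.95)] = 377 996.

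This reproduces the stated figure. At 1.7% prevalence, criteria 2 and 3 need about 25 053 and 64 197, so criterion 1 drives the size, as the article says.

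**2. Effect of a straight age term.** The documents give no age-specific rates, so these inputs are assumptions except for the mean risk:

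- mean 6-month risk 0.20%, from the Israeli data (4330 / 2 159 663 = 0.0020);
- ages 31–95, equal weight up to 55, then falling linearly;
- true log-odds slope per year of age, in four versions: (a) constant at 0.10; (b) 0.10 to age 75, then 0.06; (c) 0.11 to 70, 0.07 to 80, then 0.03; (d) 0.13 to 70, 0.06 to 80, then flat.

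A logistic model with linear age only was fitted to each curve. Predicted over observed risk by age band:

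| Age | (a) straight | (b) mild | (c) moderate | (d) strong |
|---|---|---|---|---|
| 31–44 | 1.00 | 1.41 | 1.90 | 3.02 |
| 45–54 | 1.00 | 1.19 | 1.36 | 1.72 |
| 55–64 | 1.00 | 1.02 | 1.01 | 1.05 |
| 65–74 | 1.00 | 0.88 | 0.79 | 0.70 |
| 75–84 | 1.00 | 0.91 | 0.87 | 0.82 |
| 85–95 | 1.00 | 1.15 | 1.31 | 1.57 |

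With cubic age, all bands under all four curves lie between 0.92 and 1.06.

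In absolute terms under (c), the error is 0.0234% − 0.0124% = 0.011 percentage points at 31–44, 0.2896% − 0.3657% = −0.076 points at 65–74, and 1.3543% − 1.0361% = +0.318 points at 85–95. The largest ratio therefore goes with the smallest absolute error.

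**3. Discrimination.** The age-only AUROC is the same for the linear fit and the true curve in every version (0.865, 0.837, 0.831 and 0.835). Risk never falls with age in these curves, so the ranking of patients is unchanged.

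**4. Other predictors in the model.** Adding an age-related comorbidity count, with three flattening curves, gave 1.50–2.13 at 31–44, 0.80–0.88 at 65–74, 0.73–0.90 at 75–84 and 1.12–1.36 from 85. The AUROC loss was at most 0.001. A 4-df spline brought all bands to 0.88–1.12.

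**5. The spline proposed below.** With curves that flatten after 75, linear age gave 1.46–2.12 at 31–44, 0.77–0.91 at 65–74 and 1.06–1.27 from 85. A 4-knot restricted cubic spline (3 df) brought all bands to 0.86–1.09.

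**The case against.** The strongest objection is that the preprocessing sentence concerns coding. It says that age is not categorised, and a spline also keeps age continuous. The full protocol and analysis plan are not shown, and the functional form of a predictor is often left to them. This stands in part: the article nowhere says "linear" or "main effects only", and a reader who concludes that a linear term is specified goes beyond the text. What remains is that the article does describe coding, selection method and the reason for comparing the approaches. All three lead to a single linear term, and none offers another.

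A reader might also take the statement that "machine learning methods can better handle non-linearities and interactions among variables" as an admission that logistic regression cannot handle curvature. It is a general comparison and says no such thing.

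A further objection is that misfit would show, because calibration plots, calibration slope and age-subgroup results are planned internally, with calibration plots and the subgroup analysis repeated externally. That is true, but the article does not say that the model would then be revised.

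Finally, the size depends wholly on assumed curves, and a straight curve gives no misfit. That stands, and the range reported here includes it.

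**Conclusion.** The point holds in conditional form. Followed as written, age is one linear log-odds term in both logistic models. If the true relation is straight, there is no harm. If it flattens in old age, the assumed curves give about 1.4- to 2.1-fold over-prediction at 31–44 (threefold in the strongest case), about 10–25% under-prediction at 65–84 (30% at 65–74 in the strongest case), and over-prediction from 85.

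Three stronger readings are not supported:

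- **That the model does misfit risk by age.** The documents give no age-specific rates, so this cannot be known.
- **That the comparison with random forest is biased in general.** AUROC hardly moves, so a discrimination advantage for the forest would not be explained by the form of age in these calculations. No forest was fitted in this check.
- **That age is the dominant predictor.** The article never says so; it is only the one continuous predictor named.

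This is a low-cost improvement that should be made, not an error that undermines the study.

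**What to change.** Under Data preprocessing, Prediction model development and Prediction model calculator, state that age enters both logistic models as a pre-specified restricted cubic spline, for example with 4 knots at fixed percentiles of age. Its terms should be kept together during backward selection. Do this before comparing with random forest. An age-by-sex term is optional.

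A 4-knot spline has 3 terms, 2 more than linear age. By the plan's own formula, 202 parameters need 381 776 patients and 203 need 383 666. Relative to 377 996 this is 381 776 / 377 996 = 1.010 and 383 666 / 377 996 = 1.015, so 1.0% to 1.5% more. The training part holds about 0.80 × 2 million = 1.6 million patients before the remaining exclusions. The only other cost is a slightly longer calculator formula, which stays fully transparent.
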